### Interventions

At both centres, treatment will be administered by a physician who has received prior training in a standardised protocol.

#### Treatment group: HPP group

After registration, the HPP group will receive two sessions/week of HPP for 5 weeks. For HPP, we will use JHG002, prepared at the Jaseng Namyangju Herbal Dispensary. The total treatment duration, frequency, one-time dose, and site of injection for HPP were selected with reference to previous studies [11, 15–17]. A trained doctor of Korean Medicine with at least 2 years’ clinical experience will administer JHG002 pharmacopuncture with a disposable syringe (0.5 ml) directly into the designated sites, using a standardised method. The injection sites were selected based on a textbook of acupuncture and moxibustion [17], and previous studies (Additional file 2) [18, 19]. The procedure will be performed bilaterally, irrespective of the location of pain, and at each session, 0.1 ml of JHG002 will be injected per acupoint at a total of eight locations. The dose will be adjusted in the range 0.05–0.1 ml per acupoint depending on the patient’s response (i.e. pain or discomfort).

#### Control group: PT group (TENS)

The control group will receive two sessions/week of TENS for 5 weeks as a form of PT. We will use a high-frequency, low-intensity stimulus of 50–100 Hz and up to 15 mA, so that the patients feel a current but do not feel pain. At each treatment visit, a physiotherapist will administer the treatment to the bilateral TMJ for 15 minutes. Both centres will use the same TENS device—a BioTron-DX (D.M.C, Osan, South Korea).

### Concomitant treatment

Although treatments that could affect TMD will be restricted during the treatment period (weeks 1–6), in cases where severe pain makes it unavoidable, participants may receive treatment after a subinvestigator has been informed; the treatment type and frequency will be recorded in detail in the case report form (CRF). In addition, treatments unrelated to TMD will be allowed on condition that a subinvestigator is informed of the relevant facts. No restrictions will be placed on other treatments during the follow-up period (after week 6), and regardless of allocation, both groups will receive education in the causes, prevention, treatment, and management of TMD, as well as self-stretching methods [20].

### Participants schedule

The specific participant schedule is shown in Table 1.

**Table 1 Tab1:** Participants schedule

	Study period										
Time point	Screening	Enrollment, Allocation	Active treatment after allocation					Follow-up			
	Week − 1	Week 0 (Baseline)	Week	Week	Week	Week	Week	Week	Week	Week	Week
			1	2	3	4	5	6	9	13	25
	Visit 1	Visit 2	Visit 2, 3	Visit 4, 5	Visit 6,7	Visit 8,9	Visit 10,11	Visit 12	Visit 13	Visit 14	Visit 15
Window period			±3	±3	±3	±3	±3	±3	±14	±14	±14
**Enrollment**											
Eligibility Screening	○	○									
Written informed consent	○										
Vital signs	○		○	○	○	○	○	○	○	○	○
Sociodemographic Characteristics, Medical History (e.g. neck pain, medication history)	○										
RDC/TMD test & analysis	○										
pattern Identification	○										
Laboratory test	○							○			
Randomised Allocation		○									
**Interventions**											
Treatment in JHG002 (experimental group)			← 2 times/week →								
Treatment in TENS (active control group)			← 2 times/week →								
**Assessments**											
Symptoms and change in medicine			○	○	○	○	○	○	○	○	○
NRS of TMJ pain/Bothersomeness			← Every visit →					○	○	○	○
VAS of TMJ pain	○		○	○	○	○	○	○	○	○	○
K-BDI-II			○					○		○	○
JFLS			○					○		○	○
TMJ range of motion (maximum mouth opening, mandibular excursive movement)	○		○	○	○	○	○	○	○	○	○
Compliance				○	○	○	○	○			
PGIC								○			○
EQ-5D-5 L			○			○		○	○	○	○
SF-12			○			○		○	○	○	○
Credibility and expectancy			○								
Adverse events			← Every visit →					○	○	○	○

*EQ-5D-5 L* EuroQol-5 Dimension-5 Level; *HPP* hominis placental pharmacopuncture, *NRS* Numeric Rating Scale; *PGIC* Patient Global Impression of Change; *RDC/TMD* Research Diagnostic Criteria for Temporomandibular Disorders; *PT* physical therapy; *SF-12* Short Form Health Survey 12; *TENS* Transcutaneous Electrical Nerve Stimulation; *TMJ* temporomandibular joint; *VAS* Visual Analogue Scale

### Dropout criteria

The trial may be stopped for a participant in the following circumstances:
If a severe AE is observed during the trial, or if it is believed that continuing treatment would be harmful for the participantIf the participant is discovered to have a disease that was not detected in testing before the trial, and that could influence interpretation of the study resultsIf the participant wants to stop participation during the trialIf the participant contravenes the trial plan (treatment compliance ≤ 60%)If the participant has issues with completing medical procedures for TMDIf the participant is found to be pregnant during the trialIf there are any other reasons for which a subinvestigator believes that it would not be suitable for the participant to continue the trial

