### Study design and setting

This study is a two-armed, parallel, multi-centre, randomised controlled study, and will be conducted at the Jaseng Hospital of Korean Medicine and Kyung Hee University Korean Medicine Hospital at Gangdong, located in South Korea. Prior to commencement, the study protocol has been approved by the institutional review board (IRB) at each centre (JASENG 2017–09–002-002, KHNMCOH 2019–08-002) and the Ministry of Food and Drug Safety (No. 31886). In addition, the study protocol has been registered at clinicaltrials.gov (NCT04087005) and Clinical Research Information Service (CRIS) (KCT0004437), and the state of the research will be continually updated. Information about the research centres and the researchers can be found at the trial registration site.

Participants will be recruited by physician’s recommendation, posters placed in the hospitals, and adverts placed on the hospital homepages and the metro transport system. On the first visit, a researcher will explain the study to the participants and ask them to complete and submit an informed consent form (ICF). Next, an examiner will screen the participant. Participants will be enrolled according to the inclusion/exclusion criteria, will visit 15 times, and undergo surveys either through face-to-face, telephone, or online interviews, or by distribution and return. There will be 10 treatment sessions consisting of two sessions per week for 5 weeks. Thereafter, there will be follow-up visits at 6, 9, 13, and 25 weeks from baseline. On the second visit, participants will be randomly allocated to either the HPP group or the PT group and receive the corresponding treatment. All participant management and treatment processes will be performed according to the protocol. To check compliance, we will verify whether participants adhere to the treatment schedule specified in the protocol. For the HPP group, compliance will be assessed by checking the frequency and schedule of procedures; for the PT group, compliance will be assessed by checking the frequency and schedule of TENS procedures. A study flow chart is shown in Fig. 1.

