#### Primary outcome

##### Visual Analogue Scale (VAS) of temporomandibular pain

The primary outcome is the difference in VAS for TMJ pain between baseline and the primary end point (week 6). VAS is an assessment index in which the patient records their pain on a 100 mm line from ‘no pain’ at one end, and ‘the most severe pain imaginable’ at the other end. Patients will indicate the location on the line corresponding to their TMJ pain in the last week [21].

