### Sample size

This is an investigator-initiated clinical trial, and we have calculated the required sample size with reference to similar studies and our clinical experience. First, we set a significance level of α = 0.05 (two-tailed tests), a type 2 error (β) of 0.2, and a test power of 80%. Because there are no previous studies comparing pharmacopuncture with PT for the TMJ, we selected a moderate-to-high effect size for the comparison of mean VAS between the two groups based on our clinical experience, and used Cohen’s d = 0.65 [36]. Using these parameters, we calculated the sample size using G*Power 3.1.7. Based on an effect size = 0.65, the required sample size was estimated to be 39 persons/group (total 78 persons). However, as we plan to use an analysis of covariance (ANCOVA) correcting for the outcome at baseline for our main analysis, we calculated the sample size assuming the correlation between baseline and primary endpoint to be 0.4 [(1–0.4*0.4)*78], and found that the minimum required number of participants was a total of 65 persons [37]. Thus, to account for a dropout rate of 20%, we calculated that the number of participants we need to recruit is a total of 82 persons (41 persons/group).

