### Statistical analysis

As an RCT of chronic TMD patients, this study will compare the difference within and between groups for data on efficacy, safety, and economics. The main analysis will be the ITT analysis, and a PP analysis will also be performed. The demographic results, such as sex, age, occupation, and disease history, and the treatment expectancy will be assessed by group; continuous variables will be presented as the mean ± standard deviation (SD) and categorical variables will be presented as n (%). Differences will be tested using chi-square tests and independent *t* tests. Efficacy outcomes are the changes in continuous outcomes (VAS, NRS, K-BDI, JFLS, EQ5D-5 L, SF-12) at each time point relative to baseline. The primary outcome is the change in VAS from baseline to the primary end point (week 6) in each group. For safety outcomes, we will compare the incidence of AEs between groups; after graphing all the reported ARs in participants who have received treatment at least once, we will calculate the proportion of patients who have experienced AEs in each group, and compare these using chi-square tests and Fisher’s exact test. To compare the HPP and usual care groups, for continuous variables, we will perform an ANCOVA adjusted for the baseline outcome. For categorical variables, we will use chi-square tests of Fisher’s exact test, and to analyse within-group differences between time points, we will use paired *t* tests. Additionally, we will perform an ANCOVA adjusted for baseline outcomes and covariant factors that show a statistically significant difference between the treatment groups at baseline, and we will perform a repeated measures analysis of variance (RM ANOVA) to test differences in the changes across each visit. We will perform subgroup analyses according to RDC/TMD diagnosis (Group Ia, Ib), mouth opening, and K-BDI score. Missing values will be handled in a blinded state, mainly using multiple imputation (MI), last observation carried forward (LOCF) will additionally be used, and sensitivity analyses will be performed. All statistical analysis will be performed using SAS version 9.4 statistical package (SAS Institute, Cary, NC, USA), and statistical significance will be defined as *p* < 0.05.

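### Low treatment compliance is listed as a reason to stop the trial itself for a participant, so the ITT main analysis may depend on imputed outcomes for non-compliers

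*Protocol article*

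**What the plan says.** The Dropout criteria section opens with "The trial may be stopped for a participant in the following circumstances". One listed circumstance is a participant who "contravenes the trial plan (treatment compliance ≤ 60" per cent). The same list contains the participant's own wish to leave, a severe adverse event, pregnancy, and a closing item that leaves suitability to a subinvestigator's judgement.

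Study design and setting fixes the treatment course: "There will be 10 treatment sessions consisting of two sessions per week for 5 weeks". Compliance is judged from the frequency and schedule of procedures. Table 1 records it from week 2 to week 6.

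On the endpoint, "The primary outcome is the difference in VAS for TMJ pain between baseline and the primary end point (week 6"). Table 1 schedules further VAS assessments at weeks 9, 13 and 25.

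On the analysis, the Statistical analysis section says "The main analysis will be the ITT analysis, and a PP analysis will also be performed", and "Missing values will be handled in a blinded state, mainly using multiple imputation (MI"), with LOCF used additionally and sensitivity analyses planned. The Sample size section enlarges the total "to account for a dropout rate of 20" per cent.

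**The concern.** An ITT analysis compares the groups as randomised, whatever treatment was received, and needs outcomes from poor attenders as much as from good ones. Adherence arises after randomisation. It is a natural criterion for the PP set, but a poor reason to end a participant's time in the trial.

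The reasons for missing sessions can be tied to arm and outcome: discomfort from injections, lack of benefit, or early recovery. If follow-up ends for these people, their later outcomes are missing because the protocol allowed it, not because they could not be obtained.

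The Blinding section says that neither participants nor treatment providers are blinded. A discretionary stop can therefore be applied, knowingly or not, differently in the two arms. At stake are the week 6 primary comparison, if the stop comes early, and the later outcomes, including the 6-month cost-utility analysis.

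**Working it through.** **The plan's own figures.** Inputs from Sample size: "significance level of α = 0.05 (two-tailed tests), a type 2 error (β) of 0.2, and a test power of 80" per cent, d = 0.65, baseline-to-endpoint correlation 0.4, dropout 20%.

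- Two-sample t test (noncentral t): 38.14, rounded up to 39 per group, 78 in total. This agrees with the plan.
- ANCOVA factor: (1 − 0.4²) × 78 = 0.84 × 78 = 65.52. The plan gives 65.
- Dropout: 65 / (1 − 0.20) = 81.25, rounded up to 82. This agrees.

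The plan already allows for 20% loss, so this point does not call for a new sample size.

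**Can the rule act before week 6?** Reading compliance as sessions attended out of 10, four missed sessions leave at most 6/10 = 60%, which meets the threshold. By Table 1, visits 2 and 3 fall in week 1, visits 4 and 5 in week 2, and visits 6 and 7 in week 3. Someone who attends visit 2 and misses visits 3 to 6 has reached the threshold in week 3, before the primary VAS. The article does not say when the threshold is applied. If it is applied only at week 6, the primary VAS is due at that same visit, and the loss is confined to weeks 9, 13 and 25.

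**Size, by assumption.** The article gives no non-compliance rate and no outcome for non-compliers. Let q be the share stopped in an arm, and m the amount in SD by which their benefit falls short of that of the others in the arm. The mean over the whole arm lies q × m below the mean of those observed. With the same m in both arms:

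observed-case difference − full ITT difference = (q_HPP − q_PT) × m

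For a 10-point difference, for example 20% against 10%:

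| m (SD) | shift (SD) | share of 0.65 |
|---|---|---|
| 0.25 | 0.10 × 0.25 = 0.025 | 4% |
| 0.50 | 0.10 × 0.50 = 0.05 | 8% |
| 1.00 | 0.10 × 1.00 = 0.10 | 15% |

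The sign reverses if more are stopped in the PT arm, or if those stopped did better (m negative). With equal shares and equal m the shift is zero.

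Equal shares alone do not guarantee zero. Suppose 5% to 20% of each arm are non-compliers in whom treatment has no effect. A full ITT effect of 0.65 then appears among those who remain as 0.65/0.95 = 0.68 to 0.65/0.80 = 0.81. That is an extreme assumption. It shows that the table is an illustration and not a bound.

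All these figures are for observed cases. Imputation would remove some part of the shift, and that part cannot be computed from the article.

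**The case against.** Several points on the other side stand.

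- **The rule is permissive.** A reader might infer that everyone at or below 60% is removed. The wording is that the trial may be stopped, so that reading is not supported. Discretion does not settle the matter, though, because it lets the decision depend on arm.
- **No data are deleted and nobody is excluded.** A reader might infer that outcomes already collected are discarded, or that the ITT analysis is defeated. Nothing in the article says so. Stopped participants can stay in the ITT set through imputation, with LOCF and sensitivity analyses beside it. The analysis is weakened, not voided.
- **Imputation has material to work with.** Table 1 schedules VAS in each of weeks 1 to 5 and NRS at every treatment visit. This helps for someone who misses scattered sessions. It helps least for someone who stops attending early, who may have little or no pain score after treatment began.
- **The timing of the threshold is not stated**, and six of ten sessions is a reading of it. Loss of the primary outcome is possible, not shown.
- **Power is not the issue.** With d / √0.84 = 0.709, power is about 0.80 with 65 analysed and 0.89 with all 82. A reader might charge that gap to this rule. The 20% allowance also covers withdrawal, adverse events and ordinary loss over 25 weeks, and 0.80 is the planned power.
- **An article condenses the full protocol.** Its silence on follow-up after a stop is not itself a fault. The point rests on the rule it does state, which ends the trial for the participant. The list is also mixed: its first item speaks of continuing treatment, its last of continuing the trial.

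**Conclusion.** The point holds in this form: the article makes low adherence a permitted reason to end a participant's trial, and this conflicts with an ITT main analysis. To the extent that the rule is used, the ITT result for non-compliers rests on imputed values. The usual missing-at-random assumption cannot be checked for them, because their later outcomes were never observed.

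The sign and size of any bias are unknown. The range of 0.025 to 0.10 SD assumes a 10-point difference between arms in the share stopped, a common outcome gap of 0.25 to 1.0 SD, and no correction by imputation. A reader might infer that the effect of HPP would be overstated. The documents do not support a direction, because stopping early recoverers, or stopping more of the PT arm, would push the other way.

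The matter deserves attention during enrolment, because a week 6 outcome that was not collected cannot be recovered at analysis.

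**What to change.** Amend the Dropout criteria in two respects.

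1. Remove compliance of 60% or less as a reason to end trial participation, and use that threshold only to define the PP set.
2. State that all randomised participants, including those who stop study treatment, are still assessed at weeks 6, 9, 13 and 25 unless they withdraw consent to follow-up.

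The remaining items of the list and the clinical rules for stopping treatment are not part of this change. The sample size of 82 stays.

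The cost is a protocol amendment during enrolment, which began on 17 October 2019 under approvals from both centres' review boards and the ministry, and some extra effort to complete follow-up contacts. Those contacts are already in Table 1. Study design and setting already allows telephone and online surveys, and the Discussion already plans regular phone calls to participants.

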### Outcome measure

Outcomes will be collected at different time points during a total of 25 weeks (Table 1), and the primary end point is 6 weeks after baseline.

#### Primary outcome

##### Visual Analogue Scale (VAS) of temporomandibular pain

The primary outcome is the difference in VAS for TMJ pain between baseline and the primary end point (week 6). VAS is an assessment index in which the patient records their pain on a 100 mm line from ‘no pain’ at one end, and ‘the most severe pain imaginable’ at the other end. Patients will indicate the location on the line corresponding to their TMJ pain in the last week [21].

#### Secondary outcomes

##### Numeric Rating Scale (NRS) of TMJ pain and discomfort

The extent of TMJ pain and discomfort in the last week will be assessed using NRS. NRS is a pain scale in which the patient indicates their subjective pain as a whole number from 0 to 10. The participant is asked to report their TMJ pain and discomfort using NRS, where 0 indicates ‘no pain or discomfort’ and 10 indicates ‘the most severe pain and discomfort imaginable’ [21].

##### TMJ range of motion

A TheraBite® range of motion ruler will be used to measure the range of TMJ mouth opening and excursive movement; the measurement method will follow the guidelines provided by the International RDC/TMD Consortium [22].

##### Korean version of Beck’s Depression Index-II (K-BDI-II)

The BDI-II consists of 21 questions related to sadness, guilt, suicidal ideation, and loss of interest [23]. In this study, we will use the K-BDI-II, which has been previously demonstrated to be valid and reliable by a Korean research group [24].

Each question is scored 0–3 points, and a higher total score indicates more severe depressive tendencies. A total score of 1–10 points is ‘normal’, 10–16 points is ‘mild mood disturbance’, 17–20 points is ‘borderline clinical depression’, 20–30 points is ‘moderate depression’, 30–40 points is ‘severe depression’, and ≥ 40 points is ‘extreme depression’.

##### Jaw Functional Limitation Scale (JFLS)

The JFLS [25] assesses jaw function (mastication, mobility, and emotional and verbal expression) in the last month. The assessment consists of 20 questions, each scored 0–10, where 0 points is ‘no impairment’ and 10 points is ‘very severe impairment’. In this study, we will use the official Korean version of the JFLS, which has been previously validated [26].

##### Patient Global Impression of Change (PGIC)

The PGIC assesses overall improvements in functional limitation caused by TMD. Participants rate their improvements after treatment on a 7-point Likert scale (1 = Very much improved, 4 = No change, 7 = Very much worse). Originally developed for use in Psychology, the index is now commonly used in a variety of medical fields to assess improvements in pain [27].

##### Quality of life

We will assess quality of life using the five-level version of EuroQol-5 Dimension (EQ-5D-5 L), the EuroQol vVisual Analogue Scale (EQ-VAS), and the 12-Item Short-Form Health Survey (SF-12). The EQ-5D-5 L is the most widely used method of indirectly calculating the weights of certain health states for quality of life after a multidimensional investigation of health states. It consists of five questions about current health state (mobility, self-care, usual activities, pain, anxiety/depression), and each question is scored on a 5-point Likert scale (1 = no problems, 3 = moderate problems, 5 = severe problems). We will use the Korean version of the EQ-5D-5 L, which has been previously validated [28]. The EQ-VAS [29] is an index that assesses how good or bad a patient’s health is; the patient indicates their own health status on a 100 mm vertical line, from worst health at one end to best health at the other end. The SF-12 is a shortened version of the Short Form-36 Health Survey, which is a widely used instrument to assess health-related quality of life. The SF-12 consists of 12 questions across eight domains, and higher scores indicate a better health-related quality of life [30]. In this study, we will use the Korean version of the SF-12, which has been previously validated [31].

#### Costs data

Costs consist of medical costs, non-medical costs, and costs associated with loss of production [32]. For medical costs, we will investigate costs billed at medical institutions for medical services (official medical costs), and unofficial payments made by the individual without visiting a medical institution, such as the purchase of over-the-counter drugs, health foods, and medical devices (unofficial medical costs). We will use both micro and macro estimation methods. Non-medical costs will include travel costs, time costs, and care costs associated with the use of medical services. For travel costs, two-way transport means and costs will be estimated; for time costs, the duration of consultations at medical institutions, of two-way travel, and time spent waiting for consultations will all be included; care costs will not be separately investigated. Costs associated with loss of production comprise the economic costs due to loss of labour because of disease or early death and will be investigated using the Work Productivity and Activity Impairment Questionnaire, which is an instrument used to measure loss of production. The results of the questionnaire will be converted into costs for use in the cost-effectiveness analysis.

